### Statistical analysis

To test the primary hypothesis, we will consider the clusters of prenatal clinics as the unit of analysis. We are interested in observing how the absolute difference of the percentage of women who received the 5 A’s differs between the control and the intervention group. For that reason, we will compute the outcome rate for each prenatal clinic at baseline and the follow-up periods, and then we will calculate the outcome rate change as the difference between the follow-up and baseline rates. We will apply the *t*-test to those differences in order to test the intervention effect. It has been demonstrated that the *t*-test for two samples applied to cluster rates is appropriate when the number of clusters is low [45].

For the second hypothesis, we will use the woman as the unit of analysis because we want to study the effect of the intervention on the individual. For that we will fit a model in which the variables included will be the intervention, the time (baseline and follow-up measures) and the “intervention by time” interaction. To test the effect of the intervention we will focus on the significance of the interaction. We will use a Generalized Estimation Equation (GEE) to estimate the model and we will report the effect size as OR with the 95% confidence interval. For both outcomes, we will perform an intention-to-treat analysis to compare the groups.

To test if the intervention has changed the attitudes and readiness of midwives towards providing counseling to women, we will consider the percentage of providers that reported they are planning to change their approach about tobacco with their patients in the following six months or they have already changed it in the last six months. We will use the same analytical approach that will be used for the primary hypothesis.

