### Sample size

The sample size is based on both primary and secondary objectives. A pre-test post-test (2 time–points) nested cross-sectional design was planned with 10 intervention and 10 control clinics. Each intervention and control group will contain seven clinics, with a minimum of 200 women at each time point, and three smaller clinics, with a minimum of 120 women at each time point. For each objective, the statistical power was estimated using a Monte Carlo simulation with 3,000 repetitions. In the simulation, binary outcomes from women were generated from the proposed pre-test post-test nested cross-sectional design under the following assumptions:

• An increase in the frequency of women receiving the “5 A’s” at the end of pregnancy from 10% to 20% in the control group and from 10% to 50% in the intervention group (i.e., an intervention effect of 30%) for the primary objective.

• A decrease in the frequency of women who smoke at the end of the pregnancy from 18% to 17% in the control group and from 18% to 12% in the intervention group (i.e., an intervention effect of 5%) for the secondary objective.

• An intra-cluster correlation between 2 outcomes from different women at different times (pre-test/post-test) = Intra-cluster correlation between 2 different women at the same time of 0.05. The value of the latter intra-cluster correlation coefficient was observed in a study carried out in Argentina and Uruguay [3].

For this sample size, the estimated statistical power at the 5% level of significance (2-sided) is 1.0 for the primary objective and 0.89 for the secondary objective.

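### The smoking outcome is tested by GEE on 20 clusters with no small-sample method named; with the usual uncorrected sandwich variance the real two-sided type I error is about 8-9%, and the stated power of 0.89 holds only on that test or under an unsourced ICC assumption

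*Protocol article*

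**What the plan says.** In the Protocol article, Statistical analysis, the primary outcome (receipt of the 5 A's) is analysed at cluster level. Each cluster's change in rate from baseline to follow-up enters a two-sample t-test, with the remark that this test "for two samples applied to cluster rates is appropriate when the number of clusters is low". Provider readiness is analysed in the same way.

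Smoking at the end of pregnancy is treated differently. The woman is the unit of analysis, because interest is in the effect on the individual. The model has intervention, time and their interaction: "To test the effect of the intervention we will focus on the significance of the interaction". On estimation: "We will use a Generalized Estimation Equation (GEE) to estimate the model and we will report the effect size as OR", with a 95% confidence interval. The variance estimator, working correlation and reference distribution are not named.

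Under Sample size, the "nested cross-sectional design was planned with 10 intervention and 10 control clinics". In each arm the larger clusters are "seven clinics, with a minimum of 200 women at each time point"; the other three are planned at no fewer than 120 per period. Smoking is assumed to go from 18% to 17% in the control arm and from 18% to 12% in the intervention arm, with an ICC of 0.05 both within and between periods. From 3,000 simulated trials, "the estimated statistical power at the 5% level of significance (2-sided) is 1.0 for the primary objective and 0.89 for the secondary objective". The test applied in those simulations is not named.

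**The concern.** The usual GEE sandwich variance is justified by a large number of clusters. With 10 per arm it is biased downward, and the normal reference ignores the uncertainty in estimating it. Both faults lower the p-value and narrow the CI. The small number of clusters is the same for both outcomes, yet the plan mentions it only for the primary. Wanting an effect on the individual is a reason to choose the estimand; it does not deal with the number of clusters.

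Two things are at stake. One is the error rate and CI coverage for smoking. The other is the stated power. The sample size is said to rest on both objectives, and because primary power is 1.0, smoking is the outcome that constrains the design.

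**Working it through.** **Inputs (Sample size section).** 10 + 10 clusters; per arm and period 7 × 200 + 3 × 120 = 1,760 women; Σn² = 7 × 40,000 + 3 × 14,400 = 323,200; rates 18→17% and 18→12%; ICC ρ = 0.05 within and between periods; two-sided 5%.

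**1. The stated 0.89.** The design was simulated with 20,000 to 40,000 repetitions per setting, using two ways of generating clustered binary data (beta and logistic-normal) and a logit GEE with arm, time and interaction. The uncorrected sandwich with a normal reference gives power 0.889-0.899, so 0.89 is reproduced.

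**2. Size of that test.** Under the null (18→17% in both arms) it rejects in 8.3-8.8% of trials. A rough check with equal-sized clusters shows why. The uncorrected sandwich divides by 10 where 9 is needed, so the statistic is about √(10/9) times a t on 18 df. Rejecting beyond 1.96 then means |t18| > 1.96 × √0.9 = 1.859, which has probability 7.9%. Unequal cluster sizes add a little.

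**3. Small-sample alternatives (simulated).**

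| Test | Type I error | Power |
|---|---|---|
| Uncorrected sandwich, z | 0.083-0.088 | 0.889-0.899 |
| Kauermann-Carroll type, t(18) | 0.052-0.055 | 0.84-0.85 |
| Mancl-DeRouen, t(18) | 0.041-0.043 | 0.81-0.82 |
| Sandwich GEE calibrated to exactly 5% | 0.050 | 0.83-0.84 |
| t-test on changes in cluster rates | about 0.050 | 0.71-0.75 |
| Model-based SE, z | 0.047-0.050 | 0.875-0.879 |

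**4. Closed-form check of the GEE rows.** The log odds ratio is logit(0.12) − logit(0.17) = −1.992 + 1.586 = −0.407. With v = p(1 − p) and N = 1,760, the variance per arm is

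[(1 − ρ)N(1/v0 + 1/v1) + ρΣn²(1/√v0 − 1/√v1)²] / N².

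- Control: (23,178 + 57)/3,097,600 = 0.00750.
- Intervention: (27,161 + 3,637)/3,097,600 = 0.00994.
- SE = √0.01744 = 0.132; ratio = 0.407/0.132 = 3.08.

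With the variance known, power is Φ(3.08 − 1.96) = 0.87. From the noncentral t on 18 df, power is 0.88 at critical value 1.859 (uncorrected), 0.83 at 2.101 (Kauermann-Carroll, equal clusters) and 0.80 at 2.101 × √(10/9) = 2.215 (Mancl-DeRouen, equal clusters). The order and spacing agree with the simulation.

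**5. Closed-form check of the t-test on rate changes.** The variance of one cluster's change is (1 − ρ)(v0 + v1)/n + ρ(√v0 − √v1)².

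- Control: 0.001375 (n = 200) and 0.002289 (n = 120).
- Intervention: 0.001378 and 0.002180.
- SE = √{[7(0.001375 + 0.001378) + 3(0.002289 + 0.002180)]/100} = 0.0181; ratio = 0.05/0.0181 = 2.77.
- Power on 18 df is 0.744, inside the simulated 0.71-0.75.

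**6. How far model-based standard errors depend on equal ICCs.** Let r be the between-period ICC divided by the within-period ICC. The plan assumes r = 1. Values below 1 are assumptions made here to show sensitivity. Relative to the same base, the true variance of a change is about 0.95 + (323,200/1,760) × 0.05 × (1 − r). An exchangeable model reports about 1 − 0.05(1 + r)/2. The type I error is then 2[1 − Φ(1.96/√(true/model))].

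| r | True | Model | Type I error | Simulated |
|---|---|---|---|---|
| 1.00 | 0.950 | 0.950 | 0.050 | 0.046-0.055 |
| 0.95 | 1.409 | 0.951 | 0.107 | 0.10 |
| 0.90 | 1.868 | 0.953 | 0.162 | 0.16 |
| 0.80 | 2.786 | 0.955 | 0.251 | 0.25-0.28 |

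Over the same range Mancl-DeRouen with t(18) stays at 0.042-0.049.

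**The case against.** The article names GEE and nothing about its variance. That detail often sits in an analysis plan, which is not shown here, and nothing in the text excludes a corrected sandwich or a t reference. This stands. A reader might infer that the smoking test certainly runs at 8-9%, but the document supports that only conditionally.

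A reader might also infer that 0.89 proves the uncorrected sandwich was simulated. It does not. With 3,000 repetitions and a true power of 0.879, the Monte Carlo standard error is √(0.879 × 0.121/3,000) = 0.006, so a result of 0.885 or more, which prints as 0.89 or higher, has a probability of about 16%. Model-based standard errors hold close to 5% under the plan's own correlation assumption. On that reading 0.89 is roughly right at the 5% level, so it is not established that the quoted power is wrong.

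Nor is there one corrected power. A figure near 0.80 fits only the Mancl-DeRouen correction, which is slightly conservative. And the plan does not say that 20 clusters require a small-sample method; it says that the t-test is appropriate when clusters are few.

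What remains is that deferral to an unseen plan does not settle the matter. If that plan specifies a corrected sandwich, 0.89 overstates the power of the specified test. If it leaves the uncorrected sandwich in place, the size is wrong. Only model-based standard errors keep both statements, and they need r = 1. The article sources only the within-period ICC, and the two six-month surveys are separated by the intervention phase.

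**Conclusion.** The point holds in conditional form. If the GEE uses the uncorrected sandwich with a normal reference, the two-sided type I error is about 8-9% instead of 5%, roughly 1.7 times nominal, and the 95% CI is too narrow. About half of those errors, some 4.2-4.4% against 2.5%, would be false claims of reduced smoking. Under the plan's assumptions, robust tests at or near 5% have power 0.81-0.85 by corrected GEE, or 0.71-0.75 by the t-test on changes in cluster rates. The stated 0.89 matches the uncorrected test and lies close to the model-based one, whose validity depends on an unsourced equality of ICCs.

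The figures rest on the stated cluster sizes, rates and ICC, and on two data-generating models that agree closely. Smoking is a secondary outcome. A reader should not carry this over to the primary analysis, which uses a cluster-level t-test and is unaffected.

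**What to change.** State that the GEE for smoking is clustered on the randomised unit and uses a bias-corrected sandwich variance (Kauermann-Carroll or Mancl-DeRouen) with a t reference on 20 − 2 = 18 df, for both the interaction test and the CI of the odds ratio. Alternatively, use the cluster-level t-test already chosen for the primary outcome.

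Name the test to which the secondary power refers and restate the figure under the same assumptions: about 0.84-0.85 for Kauermann-Carroll, 0.81-0.82 for Mancl-DeRouen, or 0.71-0.75 for the t-test on changes in cluster rates. Kauermann-Carroll keeps the most power, at a size slightly above 5% (5.2-5.5%); Mancl-DeRouen stays below 5%.

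The cost is a sentence of analysis wording, one restated figure, a slightly wider CI and a less favourable stated power. Data collection and trial conduct do not change.

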### Study hypotheses and aims

Our ***primary hypothesis*** is that an intervention designed to motivate, persuade, and train midwives to deliver the “5 A’s” strategy during antenatal care is feasible in public prenatal care settings in Argentina and Uruguay and will increase the frequency of women receiving tobacco use cessation counseling during pregnancy in the intervention clinics, compared to the standard in-service training practices at the control clinics. Our ***secondary hypotheses*** are that the intervention will decrease the frequency of women who smoke by the end of pregnancy, and that the intervention will increase the attitudes and readiness of midwives towards providing counseling to women in the intervention clinics compared to the control clinics.

The ***main specific aim*** of this project is to evaluate an intervention intended to increase the frequency of women that receive the “5 A’s” strategy during pregnancy. In an implementation cluster randomized-controlled trial, we will randomize 20 prenatal care settings in the Province of Buenos Aires, Argentina, and in Montevideo, Uruguay. Midwife facilitators in the 10 intervention prenatal care settings will be identified and trained on delivery of the “5 A’s” to pregnant women (training of the trainers) and on organizing the training and delivery at their facilities in order to reach all women in prenatal care. They will then disseminate and implement the program in their prenatal clinics. The intervention will be tailored by formative research to be readily applicable to local prenatal care services and to be acceptable to local pregnant women and health providers. Pregnancy-specific self-help materials will be adapted and their acceptability evaluated. The 10 prenatal care settings in the control group will continue with their standard in-service activities.

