### Participating clusters

Argentina and Uruguay are middle-income countries with a highly literate population (97% of the population >15 years). Approximately, 99% of the childbirths are attended at maternity hospitals; 70% and 50% of childbirths take place in publicly-funded hospitals in Argentina and Uruguay, respectively, which serve the most underprivileged population. Prenatal care is provided by physicians and midwives, and over 94% of pregnant women receive prenatal care during at least four visits during pregnancy (a mean of 7 visits) [29,30].

In the public health sector, prenatal care is offered at prenatal clinics within the maternity hospitals or at primary health centers associated with them. At the hospitals, prenatal care providers are mostly obstetricians or obstetrical residents assisted by midwives; while at the primary health center, both midwives and obstetricians provide prenatal care. Our research is intended to benefit the most underprivileged populations in our region; as such, this study will be conducted in a sample of prenatal clinics within public maternity hospitals in Argentina and Uruguay and/or at primary health centers. We will call these sites “prenatal clinics,” irrespective of whether they are located at a hospital or a primary health center.

We invited public prenatal clinics located at maternity hospitals or primary health centers in the metropolitan area of the Province of Buenos Aires, Argentina, and in Montevideo, Uruguay, to participate in the study. All of them have agreed to participate in this project. The eligibility criteria for these prenatal clinics include: 1) not having a smoking cessation program based on the “5 A’s” for pregnant women in place, 2) having an estimated frequency of women receiving the “5 A’s” intervention below 20%, and 3) having midwives or nurse-midwives as part of the hospital or primary health center staff.

We will collect baseline data from those pre-selected prenatal clinics. According to the results of the analysis of the baseline data collection, prenatal clinics will be excluded if the frequency of women receiving the “5 A’s” intervention is 20% or higher. Because these prenatal clinics do not have smoking cessation program in place, it is expected that none of them will be excluded by this criterion. However, the sample size of the study was increased to allow for exclusions.

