#### Training and persuasion phase

Workshop for training on the “5 A’s” and for planning the implementation strategy.

The facilitators will participate in a 1.5 day workshop conducted in either Buenos Aires or Montevideo. Prenatal clinics’ health authorities will be invited to participate or to designate a delegate. The workshops will be given in previously selected sites outside of the prenatal clinics and will be conducted by a specialized trainer in smoking cessation programs. Interactive workshops have been proven an effective strategy for guidelines implementation [41].

The objectives of the workshop will be: to train facilitators on the “5 A’s” intervention (training of the trainers); to train facilitators on the suggested strategies to implement the “5 A’s” intervention program at their prenatal clinics; and to develop a dissemination and implementation plan.

The workshop will be adapted from the current workshops delivered by the National Tobacco Control Programs in Argentina and Uruguay [42]. Suggested topics to be included are: general overview of smoking prevalence and trend in Argentina/Uruguay; health consequences of smoking during pregnancy, specifically for the mother and the newborn baby; roles of the health care provider in preventing smoking among pregnant women; current recommendations and expected situation; brief explanation of smoking as an addiction; levels of interventions to promote smoking cessation; brief intervention “5 A’s”; assessing who is ready to quit and who is not; motivational interviews; role play; medications for smoking cessation; implementing the “5 A’s” in the prenatal clinic. We will also ask participants to create a plan to implement the “5 A’s.”

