### Attitude and readiness to change

We will assess the attitudes and readiness to provide counseling for smoking cessation to women (secondary outcome) following the “5 A’s” intervention in all prenatal care providers working at participating prenatal clinics. To that purpose, a self-administered questionnaire will be designed, adapted from a questionnaire developed and used by our group to evaluate birth attendants’ readiness to change in the Guidelines Trial [28].

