#### Data collection and management

Outcome data will be collected in two six-month periods at all participating prenatal clusters: a baseline period and a follow-up period, separated by the intervention phase during which no outcome data will be collected. During the six-month data collection periods we will collect data on ≥200 women who have received prenatal care at each of the participating clinics. Outcome data will be collected in the maternity hospitals where women attending prenatal care at the participating prenatal clinics deliver. Process data will be collected during the intervention phase and only at intervention prenatal clinics.

Trained interviewers, independent of the participating prenatal clinics, will be responsible for the administration of the questionnaire to women, including obtaining the saliva samples. To allow for interviewing women within the first 12 hours after deliveries, two shifts of interviews will be organized: one in the morning and another in the evenings. The interviewers will identify all consecutive women who have undergone childbirth in the past 12 hours and who have received prenatal care at any of the participating prenatal clinics. After obtaining informed consent, they will interview each woman and obtain the saliva sample (if the woman is eligible). Demographic and childbirth data will be extracted from the clinical record. Cotinine samples will be kept refrigerated and then frozen in order to keep them in the appropriate conditions until shipment to CDC for analysis. This postpartum strategy for data collection has been proven feasible and successful in previous studies of our group [35,36].

Data will be collected on paper forms designed specifically for the study. A digital image of the interview form will be taken and sent to the local data center for data entry, but the inclusion form and the hard copy of the interview form will remain at the hospital until the end of the data collection period. With this system, it is ensured that personal identifiers will not be taken from the hospital and will be kept securely by the hospital staff.

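### The readiness outcome has no category for a change made more than six months ago and maintained, and it is a percentage of providers where the hypothesis concerns midwives

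*Protocol article*

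**What the plan says.** The Statistical analysis section defines the outcome as "the percentage of providers that reported they are planning to change their approach about tobacco with their patients". The time limits for a planned change, and for one already made, are worded thus: "in the following six months or they have already changed it in the last six months". The outcome is analysed like the primary outcome: a rate per cluster at baseline and at follow-up, the difference between the two, and a two-sample t-test on those differences.

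The section Attitude and readiness to change calls this a secondary outcome. It is assessed "in all prenatal care providers working at participating prenatal clinics", with a self-administered questionnaire that is still to be designed. No date is given for it.

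Under Data collection and management, outcome data come in "a baseline period and a follow-up period, separated by the intervention phase during which no outcome data will be collected"; each period lasts six months. In the Training and persuasion phase, "The facilitators will participate in a 1.5 day workshop". The implementation phase follows, in which facilitators may train further providers.

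Study hypotheses and aims states the hypothesis as follows: "the intervention will increase the attitudes and readiness of midwives towards providing counseling to women in the intervention clinics compared to the control clinics". Participating clusters says that at hospitals "prenatal care providers are mostly obstetricians or obstetrical residents assisted by midwives", and that at primary health centers midwives and obstetricians both provide prenatal care.

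**The concern.** The definition covers intention and recent change. It has no place for established change. A provider who began delivering the 5 A's seven months before the survey and still does so scores the same as one who has never considered it. A provider who was planning to change at baseline, then changed and kept to it, can move from ready to not ready and so count against the intervention.

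The population also shifts. The sentence in Statistical analysis sets out to test the readiness of midwives but computes a percentage of providers, and the questionnaire goes to all prenatal care providers. If all of them enter the analysis, the test does not address the hypothesis as stated.

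At stake is a named secondary hypothesis. The result could read as no effect, or in an extreme case as harm, when the training did what it was meant to do.

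**Working it through.** The article gives no rate, effect size or power for this outcome, so there is no figure to reproduce. Its power figures of 1.0 and 0.89 belong to the two outcomes measured in women. The check applies the definition literally; every input marked as assumed is illustrative.

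**1. When an adopter drops out of the window.** Let L be the months from training to the end of the intervention phase, and s the months from then to the questionnaire. A provider who changed at training, kept to it and plans no further change is counted only if L + s ≤ 6. Neither value is in the text, so both are assumed:

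| L (assumed) | s = 0 | s = 3 | s = 6 |
|---|---|---|---|
| 3 | counted (3) | counted (6) | not counted (9) |
| 6 | counted (6) | not counted (9) | not counted (12) |
| 9 | not counted (9) | not counted (12) | not counted (15) |
| 12 | not counted (12) | not counted (15) | not counted (18) |

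Brackets show L + s. The provider is missed in 9 of the 12 cells. That is a property of the assumed grid and not a probability.

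**2. Effect on the score, first illustration.** Assumed: 40% score as ready at baseline in both arms and the control arm does not move. In the intervention arm at follow-up, 60% changed at training and kept to it, 20% are planning and 20% are neither. Let f be the share of the changes that are more than six months old.

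Score as defined = 20 + 60 × (1 − f).

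- f = 0: 20 + 60 = 80%, a change of +40 points
- f = 0.5: 20 + 30 = 50%, +10 points
- f = 1: 20 + 0 = 20%, −20 points

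Counting maintained change gives 80% (+40) whatever f is. The sign reverses when 20 + 60 × (1 − f) < 40, that is, when f exceeds 2/3.

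**3. Second illustration, different assumptions.** Assumed: 30% are ready at baseline and the control arm does not move. A share c of intervention providers change at training and maintain it, all for more than six months, and 30% of the rest are ready.

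- As defined: 0.30 × (1 − c) − 0.30 = −0.30c
- Maintained change counted: c + 0.30 × (1 − c) − 0.30 = 0.70c

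| c | As defined | Maintained change counted |
|---|---|---|
| 30% | −9 points | +21 points |
| 50% | −15 points | +35 points |
| 70% | −21 points | +49 points |

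**4. Population.** If midwives are a share m of respondents and other providers show r times the midwife effect, pooling retains m + (1 − m) × r of that effect. The article gives neither m nor r. With m assumed at 1/3, the retained share is 1/3 for r = 0, 2/3 for r = 0.5 and 1 for r = 1. With m assumed at 1/2, it is 1/2, 3/4 and 1. The range runs from heavy dilution to none.

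**The case against.** The strongest reply is that the harm is conditional. A reader might infer that providers who change at training and keep it up will be scored as failures. The text does not establish that. It gives neither the length of the intervention phase nor the date of the provider questionnaire, and the operational detail on the two six-month periods concerns postpartum women. Figure 1 may show the timing but was not available to check. Providers trained later by facilitators, or planning a further change, can still be counted. This stands, and the claim has to be worded conditionally.

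A reader might also infer that only the intervention arm is affected. That is not so. The rule leaves out long-standing good practice in control clinics and at baseline in both arms, and control clinics hear the same presentation of the national guidelines. What can be said is that training makes the misclassification probably larger in the intervention arm at follow-up.

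On population, the sentence in Statistical analysis opens with midwives, so providers could be read as referring back to them, and the survey of all providers contains the midwives in any case. The remark about obstetricians covers hospitals only; the Uruguayan clusters are primary health center clinics, and the Argentine clusters include such clinics. Nor can one assume that physicians will not respond, because the awareness seminar addresses physicians, nurses and midwives. These points rule out any firm dilution figure. They leave the mismatch between hypothesis, survey and percentage in place.

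None of this supplies the missing category. That gap is in the definition itself.

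**Conclusion.** Two defects stand on the text. The readiness definition has no category for change made more than six months earlier and maintained. The hypothesis concerns midwives, while the survey covers all prenatal care providers and the outcome is worded as a percentage of providers.

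The first defect matters for providers surveyed more than six months after they changed. This is plausible for early-trained facilitators, provided the statement that no outcome data are collected during the intervention phase also governs the provider questionnaire. The bias is then towards no effect. A reversed sign is possible but should not be presented as expected: in the first illustration it needs more than two thirds of the changes to be older than six months, and all the percentages are assumed. The amount of dilution from pooling cannot be stated from the article.

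This is a moderate point. It affects one secondary outcome, lies outside the power calculation and leaves the primary outcome untouched. It should still be settled before the questionnaire is fielded, because without an answer option for earlier change the information may not be recoverable.

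**What to change.** Score as ready any provider who plans to change within six months, or who has already changed, at whatever earlier time, and still maintains the change. The condition of maintenance is needed; without it, providers who changed and then lapsed would count as ready. Put a matching answer option in the questionnaire, and state when it is given at baseline and at follow-up.

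For the population, either analyse midwives for the stated hypothesis with all providers as a supportive analysis, or reword the hypothesis to cover all prenatal care providers. Either choice reconciles the sections.

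The cost is a change of definition and probably one answer option. Two drawbacks should be accepted knowingly:

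- The baseline rate may rise, leaving less room for improvement. The article cites a survey in which 88.9% of obstetrician/gynecologists already always or almost always advised stopping, although such advice is less than the full 5 A's.
- The midwife analysis has fewer respondents per clinic. The article expects about 8–10 facilitator midwives per clinic. If only that many midwives answered in a single-clinic cluster, one answer would move the cluster rate by 100/10 = 10 to 100/8 = 12.5 points.
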